### Harms {#22}

This is a low-risk study, and serious adverse events are unlikely. All deaths of enrolled participants will be reported to the local ethics committee and the DSMC.

## Statistical analysis {#20a, 20b, 20c}

### Definitions

Gestational age at birth is determined by subtracting the date of the dating ultrasound from the date of birth and then adding the gestational age assessed during that dating procedure, which follows the INTERGROWTH-21 protocol [72, 73]. Preterm births are defined as births occurring at < 37 completed weeks of gestation. Birth weight centiles are calculated using the INTERGROWTH-21 standard using weight captured within 72 h of birth and gestational age at birth [1]. SGA is defined as birth weight < 10th centile using the INTERGROWTH-21 standard [1].

Weight-for-age, length-for-age, and weight-for-length *z* scores are calculated based on weight and length measured at 12 months (± 28 days).

Proportion stunted, underweight, and wasted will be defined as having length-for-age *z* score < − 2 SD, WAZ < − 2SD, and weight-for-length *z* score < − 2SD, respectively, using WHO standards [56]. The neurodevelopmental outcome will be the composite scores of cognitive, language, motor, and socio-emotional scales and scaled scores of receptive language, expressive language, fine motor, and gross motor domains of BSID-III at 12 months of age.

#### Comparability between the two arms

Summary values (means, centiles, proportions) for sociodemographic characteristics in both arms will be presented in the baseline table.

### Main effects

The primary outcome will be analyzed using an intention-to-treat (ITT) approach. All participants randomized to a treatment group will be included in the analysis, regardless of their adherence to interventions. However, missing data on the primary outcome at 12 months will not be imputed since the key assumption that data will be missing at random would probably not be valid. However, we will use imputation methods depending on the nature of missingness for the secondary outcomes. Some authors might call the above approach modified intention-to-treat analysis; however, there is no clear consensus on the use of this terminology as per the CONSORT guidelines. The statistical precision of the effects will be presented as 95% confidence intervals (Cis). The distributions of WAZ will be presented in Epanechnikov kernel density plots by study arms. To quantify any differences in distribution, the 5th, 10th, 15th, 20th, and… up to the 95th percentiles will be compared using quantile regression. The 95% CI of the difference between the percentile estimates for the two arms will be calculated using bootstrap resampling with 1000 replacements. The percentile differences and corresponding CIs will be visualized in forest plots.

For binary outcomes, we will use generalized linear models (GLMs) of the binomial family with a log-link and an identity-link function to calculate the relative risks and risk differences, respectively. For continuous outcomes, GLMs of the Gaussian family with an identity-link function will be used to calculate the difference in means between the groups.

The effect of the intervention package on infant mortality across both strata will be estimated in a Cox proportional hazards model taking the stratification variable into account. The days of follow-up for each infant will be calculated as the date of enrolment subtracted from the date of the last follow-up or death.

We will adjust for imbalances in baseline features if present.

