### Recruitment {15}

Accounting for a possible 20% loss to follow-up from enrolment to 12 months of age, we will need 650 infants per arm per stratum. We will therefore enroll a total of 2600 infants (1300 preterm and 1300 term SGA).

With 650 infants in each stratum in each arm, assuming a prevalence of underweight of 25% in the control arm at 12 months of age, we will be able to detect a 30% relative reduction in underweight, with 90% power and 95% confidence level. A narrow effect size in the hypothesis has been considered to adjust for some earlier impact of similar intervention in the study area, by our team [1]. We will also be able to detect a difference of 3 composite standard score–points (0.2 SD) in the domains of the Bayley Scales of Infant and Toddler Development, 3rd Edition (BSID-III).

Assuming 25% of babies are term SGA and 15% preterm, and 40% attrition from pregnancy identification to enrolment, we will probably need gestational age assessment through dating ultrasounds in ~13,000 pregnancies [1]. The sample size estimation for this study was conducted using *power* commands in STATA.

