### Outcome measures {12}

The primary outcomes include attained weight, and weight for age *Z* scores at 12 months of age.

The secondary outcomes along with timing of their measurements are listed in Additional file 4. The key secondary outcomes for children are proportion stunted, wasted, and underweight at 6 and 12 months; overweight or obesity at 12 months; weight and length velocities between birth to 6 months and 6 to 12 months; neurodevelopment (composite cognitive, language, motor, socio-emotional, temperament and HOME scores; Mean Global Scale for Early Development score) at 12 months [62]; morbidity and hospitalization from birth to 12 months; and dietary assessment, micronutrients, and anemia status at 12 months (in a sub-sample).

The key secondary outcomes for mothers (Additional file 5) are depressive symptoms, nutritional status during the postpartum period, and household consumption and expenditures at 6 and 12 months of infant age, as well as dietary assessment at 3 and 6 months (in a sub-sample).

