### Weight and length growth trajectories between birth and 12 months

A linear mixed-effects regression model with an unstructured covariance matrix will be used to examine the effect of the intervention on weight and length velocity from birth to 6 months and 6 to 12 months [74]. The effect of intervention on secondary outcomes will be assessed using the same methods as for the primary outcomes.

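### Doubt about missing-at-random does not justify a complete-case primary analysis that leaves the earlier weights out of the 12-month contrast

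*Protocol article*

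**What the plan says.** Under Outcome measures {12}, "The primary outcomes include attained weight, and weight for age" z score at 12 months. Main effects declares intention-to-treat: "All participants randomized to a treatment group will be included in the analysis, regardless of their adherence to interventions". It then says that "missing data on the primary outcome at 12 months will not be imputed since the key assumption that data will be missing at random" is unlikely to hold, and concedes that some would call the result modified intention-to-treat. For continuous outcomes, "GLMs of the Gaussian family with an identity-link function will be used to calculate the difference in means between the groups". No earlier weight is named in that model; the only adjustment mentioned is for baseline imbalances, if any appear.

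For secondary outcomes the same paragraph says "we will use imputation methods depending on the nature of missingness for the secondary outcomes". The growth-trajectories section adds: "The effect of intervention on secondary outcomes will be assessed using the same methods as for the primary outcomes".

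On the amount of loss, Recruitment {15} says: "Accounting for a possible 20% loss to follow-up from enrolment to 12 months of age, we will need 650 infants per arm per stratum".

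Weight is measured within 72 hours of birth at screening, before randomization (Surveillance, follow-up, screening, and enrollment), and at 1, 3, 6, 9 and 12 months in both arms (Outcome ascertainment {18a}). A linear mixed model with unstructured covariance is planned for weight and length velocity. Outcome ascertainment {18a} also says that participants who stop the intervention are censored and analysed only up to that point.

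**The concern.** The reason given does not support the choice made. Not imputing does not avoid an assumption about missing data; it substitutes another. If loss depends on earlier weight, and does so differently in the two arms, the complete-case difference is biased, whereas an analysis that conditions on the earlier weights is not. If loss also depends on the unseen 12-month weight, both can be biased, and dropping the earlier weights gives no protection.

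The text is also at odds with itself in four places:

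- It promises to analyse everyone randomized, but its rule excludes infants without a 12-month weight.
- The censoring of infants who stop the intervention does not fit with analysis regardless of adherence, and could create further missing 12-month values.
- A likelihood-based mixed model normally rests on MAR, so the plan accepts for velocity what it rejects for attained weight.
- Underweight is defined as WAZ below −2. The text permits imputation of 12-month underweight, conditionally, but not of the WAZ from which it is derived.

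At stake is the primary estimate in both strata. Study teams cannot be masked and contact intensity differs greatly: the intervention arm has 11 visits in the first 28 days and regular visits afterwards, against routine government home visits in the comparison arm. Loss that works differently by arm is therefore plausible.

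**Working it through.** **1. The plan's own figures.** Inputs from Sample size {14} and Recruitment {15}: 0.20 SD difference, 90% power, 95% confidence (taken as two-sided alpha 0.05), 20% loss.

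- The t-based sample size is 526.3, rounded up to 527 per arm. This matches the plan.
- 527 / 0.80 = 658.75, so 659, against the stated 650 (1.4% apart).
- Missing at the full allowance: 650 × 0.20 = 130 per arm, or 260 per stratum. Remaining: 520 per arm, with power 0.897.

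Power is essentially preserved, so the question is bias.

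**2. Bias by arithmetic.** Let p be the fraction missing in an arm and g the amount by which lost infants are lighter than observed ones (in SD). The observed mean exceeds the full-arm mean by p × g. With C for control and I for intervention, the complete-case difference understates the effect by

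p_C × g_C − p_I × g_I.

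The gaps are assumptions; the protocol gives none.

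| Assumed loss (C / I) | Assumed gap (C / I) | Bias | Share of 0.20 SD |
|---|---|---|---|
| 20% / 20% | 0.3 / 0 | 0.20 × 0.3 − 0 = 0.06 SD | 30% |
| 25% / 15% | 0.3 / 0.3 | 0.075 − 0.045 = 0.03 SD | 15% |
| 20% / 20% | 0.3 / 0.3 | 0.06 − 0.06 = 0 | 0% |

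If the gap in the first row were in the intervention arm instead, the sign would reverse and the effect would be overstated. For scale, the standard error with 520 per arm is √(2/520) = 0.062 SD.

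**3. Simulation.** Settings: 650 per arm, 20% missing in each arm, true effect 0.20 SD, 2000 repetitions. Dropout slopes (log-odds per SD) and the correlation between earlier and 12-month weight are assumptions.

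| Dropout depends on | Arms (slope) | Correlation | Complete case | Using the earlier weight |
|---|---|---|---|---|
| 9-month weight (MAR) | control only (−0.5) | 0.7 / 0.8 / 0.9 | 0.133 / 0.123 / 0.113 | about 0.20 each |
| 9-month weight (MAR) | both (−0.5) | 0.7 to 0.9 | about 0.20 | 0.20 |
| 12-month weight (not MAR) | control only (−0.5) | 0.8 | 0.105 | 0.165 |
| 12-month weight (not MAR) | both (−0.5) | 0.8 | 0.20 | 0.20 |
| 12-month weight (not MAR) | control only (−0.5) | 0.3 (early weight only) | 0.105 | 0.113 |

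In the second row the empirical standard error falls from 0.061–0.063 to 0.057–0.058 when the earlier weight is used.

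**4. Reading.** Using the earlier weight was never worse in these settings. It removes the bias when loss is explained by that weight, and removes part of it when MAR fails and the last weight is recent. It does little when only an early, weakly correlated weight is available. If the 9- and 12-month values correlate at 0.8 to 0.9 (assumed), the 9-month weight explains 0.8² = 64% to 0.9² = 81% of the 12-month variance, but only for infants lost after month 9.

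**The case against.** The strongest defence is that the target is a difference between arms. Complete cases give an unbiased difference whenever selection acts alike in both arms, even when loss depends on the 12-month weight itself. That stands. A reader might infer that the complete-case estimate is valid only under missingness unrelated to weight, or that the primary result will be biased. The documents support neither. An independent team makes the same five outcome visits in both arms and is kept unaware of allocation as far as possible, which limits differential loss without excluding it.

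Other limits also stand:

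- The 20% is a possible loss used for planning, not a forecast.
- A reader might infer that the repeated weights are ignored altogether. They are analysed for velocity, and baseline adjustment could bring in birth weight; they are absent only from the primary contrast as written.
- A reader might infer that underweight will be imputed and WAZ will not. Imputation of secondary outcomes depends on the nature of missingness, so underweight might be left unimputed too. The sentence on using the same methods may refer to the regression models only.
- A statistical analysis plan that is not shown may add sensitivity analyses, so their absence from the article is not counted here.
- A model using all randomized infants could silently supply 12-month weights for infants who died.

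None of this rescues the stated reason. The article fixes the primary rule and its justification, and the justification does not lead to the rule.

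**Conclusion.** The point holds in this form: the plan rejects imputation because MAR is doubtful, but its complete-case contrast needs either no relation between missingness and 12-month weight within arm or cancellation between arms. Doubt about MAR supports neither condition and gives no ground for leaving the earlier weights out. The exclusion also contradicts the statement that everyone randomized is analysed.

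The size cannot be read from the documents. Under the assumptions above, the bias runs from zero (selection alike in both arms) through 0.03 and 0.06 SD in the arithmetic examples to 0.07–0.09 SD in the simulated control-only MAR case (0.20 − 0.133 to 0.20 − 0.113). The benefit of the earlier weights is largest for late losses and small for early ones. The handling of WAZ and underweight is an ambiguity to close, not a proven discrepancy.

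**What to change.** 1. Within each stratum, estimate the primary 12-month contrast either from a mixed model with unstructured covariance, as already planned for velocity, or from multiple imputation by arm. Use birth weight as a baseline covariate, since it precedes randomization, together with the 1, 3, 6 and 9-month weights.
2. State that weights are not imputed after death, and report deaths separately by arm.
3. Address the worry that data are not MAR directly, with a delta-adjusted (tipping-point) sensitivity analysis. Keep complete case as a supporting analysis.
4. Apply one missing-data rule to WAZ and to the underweight indicator derived from it.
5. Reconcile the statement in Main effects that everyone randomized is analysed with the censoring sentence in Outcome ascertainment {18a}, and say whether the sentence on the same methods for secondary outcomes covers missing data.

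No new measurements are needed, because these weights are already scheduled in both arms. The cost is some extra programming and a primary estimate that depends on a model.

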### Sample size {14}

There are two strata: preterm and term SGA. Sample sizes are calculated for 90% power and 95% confidence for each stratum. Assuming a minimum of 0.20 SD mean difference in weight (which translates to a 200 g weight difference) or WAZ scores between the intervention and control arms at 12 months, a total of 1054 infants per strata, i.e., (527 infants per arm per strata) are required [5].

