**Fig. 1 Fig1:**
[figure not shown]
Trial profile

During follow-up, pregnant women are counselled by field assistants (FAs) to register and deliver in a hospital, attend regular antenatal care clinics, consume an adequate diet, recognize danger signs in pregnancy, and initiate of breastfeeding early after birth. The field assistants periodically contact the identified women over the phone (through home visits if phone calls are unsuccessful), more frequently in the last trimester. For all live births, the team measures the baby’s weight within 72 h of birth and screens using inclusion and exclusion criteria. If the inclusion criteria are met, there are no exclusion criteria, and consent is given; the mother-infant pair is randomized to the intervention or control arm in the relevant stratum (preterm or term SGA). Post enrollment, baseline information is collected, including sociodemographic characteristics and recent childbirth related details including care received after delivery.

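### Covariate adjustment is triggered by chance baseline imbalance, so the primary model depends on the data and most of the precision available from birth weight and gestational age is lost

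*Protocol article*

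**What the plan says.** The protocol article, Outcome measures, reads: "The primary outcomes include attained weight, and weight for age *Z* scores at 12 months of age". Each stratum (preterm, term SGA) has its own primary objective and its own sample size.

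For continuous outcomes, Main effects says that "GLMs of the Gaussian family with an identity-link function will be used to calculate the difference in means between the groups". No covariate is named there. The section closes with a sentence of its own: "We will adjust for imbalances in baseline features if present". The article does not say what counts as an imbalance, which features are candidates, or whether an adjusted estimate would replace or accompany the unadjusted one. The subsection on comparability of the arms mentions only sociodemographic characteristics for the baseline table.

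The main growth-related baseline variables are known before allocation. Under Surveillance, follow-up, screening, and enrollment, the team measures "weight within 72 h of birth and screens using inclusion and exclusion criteria". Gestational age comes from the dating ultrasound and is needed to assign the stratum.

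**The concern.** Allocation is by permuted blocks through a web-based system, so a difference between arms at baseline is chance. Observed imbalance is therefore a poor reason to choose a covariate. What matters is whether the variable predicts 12-month weight, and that can be judged in advance.

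The stated rule has two consequences. First, the model behind the primary estimate is not fixed until the baseline data have been seen, and it may differ between two strata that are meant to answer the same question. Second, prognostic variables enter the model only when they happen to be imbalanced, so in most realisations of the trial their precision is not used.

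This differs from leaving a covariate list to the statistical analysis plan. The article states a rule for choosing covariates, and a later plan would have to follow it or overrule it.

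**Working it through.** **Inputs from the protocol article.** The Sample size section sets 90% power with a 5% error level in every stratum. It describes the target effect as follows: "Assuming a minimum of 0.20 SD mean difference in weight (which translates to a 200 g weight difference) or WAZ scores". From these it derives 1054 infants per stratum, that is, 527 in each arm. Recruitment section: 650 enrolled per arm per stratum, 20% loss, so 650 × 0.80 = 520 analysed per arm.

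**Assumed inputs.** R², the share of 12-month outcome variance explained by the covariates within a stratum, is not in the documents; 0.05 to 0.30 is shown. The imbalance criterion is also not given; p < 0.05 per covariate is assumed.

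**Step 1: the plan's own figure.** n per arm = 2(z₀.₉₇₅ + z₀.₉₀)²/δ² = 2 × (1.960 + 1.282)²/0.20² = 525.4, rounded up to 526. The t-based version gives 526.3, rounded up to 527, which is the stated number. It reproduces with no covariate adjustment, so the design takes no credit for baseline covariates.

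**Step 2: always adjusting, 520 per arm.** SE = √[2(1 − R²)/520] in SD units; power = Φ(0.20/SE − 1.960).

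| R² | SE | Power | n per arm for 90% power |
|---|---|---|---|
| 0 (unadjusted) | 0.062 | 89.7% | 526 |
| 0.05 | 0.060 | 91.1% | 500 |
| 0.10 | 0.059 | 92.5% | 473 |
| 0.20 | 0.055 | 95.0% | 421 |
| 0.30 | 0.052 | 97.1% | 368 |

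**Step 3: how often chance pulls the trigger.** With k independent covariates, P(at least one flagged) = 1 − 0.95^k. This is 14% for k = 3 and 40% for k = 10.

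**Step 4: adjusting only when imbalanced.** Simulation with 400,000 runs, 520 per arm, three independent covariates sharing R² equally, and each covariate entered only if flagged.

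| R² | Power, never adjust | Power, adjust if imbalanced | Power, always adjust | Type I error, adjust if imbalanced |
|---|---|---|---|---|
| 0.10 | 89.7% | 90.1% | 92.5% | 4.7% |
| 0.20 | 89.8% | 90.6% | 95.0% | 4.5% |
| 0.30 | 89.7% | 90.9% | 97.1% | 4.2% |

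At R² = 0.20 the triggered rule gains about 0.8 points of the 5.2 available, roughly one sixth. The proportion is similar in the other rows. Type I error stays below 5%.

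**The case against.** The strongest reply is that nothing here is invalid. An unadjusted randomised comparison is unbiased, the sample size was built for it, and 89.7% is the 90% target to within rounding. Unused precision is a lost opportunity and not an error. The closing sentence also stands after the mortality paragraph without naming an outcome, so it could describe a sensitivity analysis, and a statistical analysis plan that is not shown may settle this. All of that is fair, and it limits the weight of the point. It does not rescue the rule: the sentence sits in the section that governs the primary outcome, exempts nothing, and makes adjustment conditional on the data.

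The size of the gain is also uncertain. Term SGA infants are by definition below the 10th birth-weight centile and at 37 weeks or more, and preterm infants are all below 37 weeks, so R² within a stratum may be small. WAZ is already standardised for age and sex, so sex should add little there.

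Two stronger readings are tempting, and the documents support neither.

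- A reader might infer that the rule inflates type I error. Applied mechanically it is slightly conservative (Step 4). Only if the unadjusted or the fully adjusted result could be claimed at will does the error rise, to 6.4%, 7.1% or 7.5% at R² of 0.10, 0.20 or 0.30 in the same simulation. The article does not define the rule tightly enough to exclude this, but it does not say that either result may be claimed.
- A reader might notice that at R² = 0.20 the effective size is 520/0.80 = 650, the number enrolled, and infer that adjustment makes good the 20% loss to follow-up. The match comes from choosing 0.20. Smaller standard errors also do not repair data that the article itself expects not to be missing at random.

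**Conclusion.** The point holds as a weakness in pre-specification and efficiency. The primary model for weight and WAZ depends on chance imbalance and may differ by stratum, and under the assumed trigger most of the precision from variables already in hand is lost. The trial is not invalidated or underpowered by this: the unadjusted analysis has about 90% power.

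The data-dependence follows directly from the stated sentence. The size of the gain does not: 1.4 points of power at R² = 0.05 (91.1 − 89.7), rising to 7.4 points at 0.30 (97.1 − 89.7), is an illustration on an assumed range, and the truth may lie at the low end. The change is worth making because it costs almost nothing.

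**What to change.** Delete the conditional sentence. State instead that, in each stratum, the primary linear model for 12-month weight and for WAZ includes arm, birth weight (or birth-weight z-score) and gestational age at birth, with sex added for attained weight in kg, whatever the observed balance. Report the unadjusted difference as supportive, and choose no covariate on observed imbalance.

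Keep age at measurement out of the primary model. Z-scores are "calculated based on weight and length measured at 12 months (± 28 days"), so age at the visit can vary, but it is observed after randomisation and is not a baseline variable. Use it only in a sensitivity analysis for weight in kg.

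The cost is wording in the protocol and, if one exists, the analysis plan, settled before data are compared by arm. Birth weight and gestational age are already collected, and sex is needed to compute WAZ on the WHO standards. Sample size and procedures do not change.
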